# A phase II pilot randomized controlled trial to assess the feasibility of the “supra-marginal” surgical resection of malignant glioma (G-SUMIT: Glioma supra marginal incision trial) study protocol

**DOI:** 10.1186/s40814-022-01104-1

**Published:** 2022-07-05

**Keywords:** High-grade gliomas, Supra-marginal resection, Malignant brain tumor

## Abstract

**Background:**

High-grade gliomas are the most common primary malignant brain tumor in adults having a median survival of only 13–16 months. This is despite the current standard of maximal safe surgical resection followed by fractionated radiotherapy and chemotherapy. Extending the tumor resection limit beyond the gadolinium (GAD)-enhancing margin (i.e., supra-marginal resection) could in principle provide an added survival benefit as it has been shown that > 80% of post-operative tumor recurrence is within a 2-cm region surrounding the original GAD-enhancing margin. However, this must be weighed against the risk of potential damage to functional brain tissue.

**Methods:**

In this phase II pilot randomized control trial (RCT), we aim to assess the feasibility of “supra-marginal” resection extending 1 cm beyond the enhancing tumor in adults with radiographic evidence of GAD-enhancing intra-axial tumor consistent with high-grade glioma in a safe anatomical location and a Karnofsky Performance Score > 60. With six academic institutions with established neurosurgical oncology practices in participation, we aim to enroll 72 patients over 2 years. Primary outcomes include evaluating the feasibility of performing a large-scale trial with regard to recruitment, allocation, and outcome documentation as well as safety data. Secondary outcomes include determining if there is an increased survival benefit with supra-marginal resection and impact on quality of life (Modified Rankin Scale (mRS), EuroQol-5D (ED-5D), 30-day all-cause mortality).

**Discussion:**

Recent studies have revealed survival advantages comparing supra-marginal resection to standard attempt at gross total resection (GTR) with no additional perioperative surgical risk; however, the current quality of evidence is low and under-powered. Therefore, there are no current practice guidelines, and the philosophy of surgical resection is guided by individual surgeon preferences on an individual patient basis. This creates additional uncertainty and is potentially detrimental to our patients. This clinical equipoise supports the need for an adequately powered RCT to determine whether a supra-marginal resection can have a positive impact on survival for patients with HGGs. Our pilot RCT will test the feasibility of comparing the standard gross total resection of GAD-enhancing tumors and supra-marginal resection to prepare for a larger definitive multicenter RCT.

**Trial registration:**

ClinicalTrials.gov, NCT04737577. Registered on February 4, 2021

**Supplementary Information:**

The online version contains supplementary material available at 10.1186/s40814-022-01104-1.

## Introduction

High-grade gliomas (HGGs, WHO grade III–IV gliomas) are the most common primary malignant brain tumor in adults [1, 2]. The median survival is only 13–16 months, despite the current standard of maximal safe surgical resection followed by a combination of fractionated radiotherapy and chemotherapy [3, 4]. GTR defined as resection of the GAD contrast-enhancing regions, is an established prognostic marker of overall survival and part of the current standard of care [5, 6]. A meta-analysis of 37 studies (41,117 patients) demonstrated higher 1-year overall survival following GTR compared with subtotal resection (RR 0.62, 95%CI, 0.56–0.69; *P* < .001) [7]. A personalized survival modeling study based on 830 patients demonstrated that *any incremental increase* in the extent of tumor resection improved overall survival [8]. A post hoc analysis of the landmark trial establishing the current standard of care showed that patients in whom GTR was possible gained an additional 4.1 months of survival with adjuvant temozolomide treatment, whereas those with a subtotal resection only gained an additional 1.8 months with this therapy [9]. Maximizing resection of GAD-enhancing regions directly impacts survival while improving the efficacy of modern adjuvant treatment as well [10].

The highly infiltrative nature of HGGs, with histological invasion extending beyond the GAD-enhancing margin on magnetic resonance imaging (MRI), is a known challenge in HGG surgery [11–14]. Therefore, the current definition of GTR based on MRI findings is misleading. It has been shown that > 80% of post-operative tumor recurrence is within a 2-cm region surrounding the original GAD-enhancing margin on MRI [4]. However, there is no consensus on the optimal resection margin beyond the GAD-enhancing region on MRI. Current recommendations regarding the size of the resection margin range from 0.5 to 3.0 cm beyond the GAD-enhancing region [15–17]. Extending the tumor resection limit beyond the GAD-enhancing margin (i.e., supra-marginal resection) could in principle provide an added survival benefit; however, this must be weighed against the risk of potential damage to functional brain tissue. Leveraging the knowledge that certain brain regions are less functional and potentially more amenable to a supra-marginal resection, the adoption of a more aggressive surgical strategy can be conceived in favorable anatomical locations. A meta-analysis based on seven low-quality studies (88 patients total)—none randomized—demonstrated a trend toward improved overall survival favoring a supra-marginal HGG resection, but was limited by failure to measure neurological and functional status in the majority of patients [18].

Clinicians must balance any potential survival benefits of the extent of surgical resection in HGG with the competing risk of potential surgical complications. While a more aggressive philosophy of surgical resection in well-selected patients can potentially improve survival, the potentially added risk of neurological deficit, which could in turn affect the quality of life (QOL) and eligibility for adjuvant therapy, must also be considered. We conducted an independent systematic review of the literature to search for studies investigating whether survival is improved with the extension of surgical resection beyond the enhancing margin of tumor and associated surgical risks. In order to achieve maximal sensitivity, we used a broad search strategy combining terms related to the condition (glioblastoma, high-grade glioma, malignant glioma) with terms describing the extent of surgical resection (marginal, beyond enhancing margin, supra-marginal, MR flair signal margin). Very few studies have examined these risks in detail [18, 19]. Two recent studies evaluated outcomes in a total of 51 patients with supra-marginal resection. One study was a parallel-group prospective study, and the other was a retrospective case series. Both studies revealed survival advantages compared to standard attempts at gross total resection with no additional perioperative surgical risk [20].

The evidence for supra-marginal resection thus far is low-quality and under-powered [18]. Therefore, there are no practice guidelines, and the philosophy of surgical resection is guided by individual surgeon preference on an individual patient basis. This creates additional uncertainty and is potentially detrimental to our patients. In preparation for this pilot study, we have also conducted a survey of Canadian neurosurgeons to evaluate the specialty’s perspective on supra-marginal resections. The most compelling result was that 90% of participants were willing to consider enrolling patients in a randomized controlled trial comparing supra-marginal vs conventional marginal resection (Additional file 6). Together, these findings demonstrate clinical equipoise, supporting the need for an adequately powered RCT to determine whether a supra-marginal resection can have a positive impact on survival for patients with HGGs.

## Objectives

The objective is to conduct a pilot RCT to test the feasibility of comparing the supra-marginal and standard resection approaches in a larger multicenter phase III RCT. The primary feasibility outcome is the number of patients enrolled and successfully allocated to the study interventions per year during the duration of the pilot RCT at each study center.

## Trial design

A randomized (1:1) pilot RCT conducted at six (6) academic institutions with established neurosurgical oncology practices.

## Methods: participants, interventions, and outcomes

### Eligibility criteria

The following are the inclusion criteria:i)Radiographic evidence of a GAD-enhancing brain tumor consistent with HGG.ii)Age ≥ 18 to < 80 years.iii)Karnofsky Performance Score ≥ 60.iv)The tumor is in an anatomical location that is considered safe for surgical resection (Additional file 1).

The following are the exclusion criteria:i)Multi-focal tumor, gliomatosis cerebri (≥ 3 lobes of the brain affected), and tumors crossing the midline or with leptomeningeal enhancementii)Previous craniotomy for tumor excision (stereotactic biopsy is permitted)iii)Intraoperative histopathological diagnosis not consistent with HGGiv)Known metastatic cancerv)Uncorrectable coagulopathyvi)Unable to obtain GAD-enhanced brain MRI

The selection of surgeons for this trial will be based on the criteria to demonstrate an adequate level of surgical expertise for the resection of HGGs (Additional file 2). Figure 1 illustrates a guide for safe anatomical tumor locations amenable to standard GTR and supra-marginal resection.

**Fig. 1 Fig1:**
[figure not shown]
Safe anatomical tumor locations guide. Safe tumor locations include the right and left frontal (excluding supplementary motor area, motor cortex, and Broca’s area), right and left temporal (excluding superior temporal gyrus with the maximal extent of resection posteriorly from the temporal pole of 4–5 cm), and right and left occipital lobes. Increasingly safe regions are indicated in red

### Recruitment

Research coordinators in each participating center will screen the patients for eligibility in neurosurgical clinics or in the neurosurgical hospital ward on a daily basis for eligibility. Each eligible participant will have the option of connecting support group(s) to allow mutually satisfied discussion and a more comfortable and informed decision to participate. The reasoning for the non-enrollment of eligible patients (either patient or physician related) will be recorded at each center.

### Ethics approval and consent to participate

This study is conducted in accordance with the principles set forth in the Belmont Report: Ethical Principles and Guidelines for the Protection of Human Participants of Research and codified in the Tri-Council Policy Statement and/or the ICH E6.

The study protocol, informed consent form(s), recruitment materials, and all participant materials have been approved by the Ontario Cancer Research Ethics Board (CTO Project ID: 3297).

Prior to involvement in any study-related activities, consent will be obtained in writing for each participant using the current Research Ethics Board (REB)-approved informed consent form. Participants will be given the opportunity to discuss the study with their surrogates or think about it prior to agreeing to participate. They may withdraw consent at any time throughout the course of the study.

### Interventions

#### Explanation for the choice of comparators

This pragmatic RCT is comprised of 2 arms:Supra-marginal resection (intervention arm): planned resection extending beyond the ≥ 95% periphery of the GAD-enhancing region to either at least 1 cm into non-enhancing tissue or to the nearest non-enhancing sulcal boundary/ventricle wall, if these structures are closer than 1 cmMarginal (i.e., GTR) resection: planned resection extending only to ≥ 95% of the GAD-enhancing regions of the tumor without expanding the resection beyond this margin.

#### Intervention description

##### Rationale for supra-marginal definition

More than 80% of HGG tumors recur within a 1–2-cm margin of the original GAD-enhancing regions, and histopathological infiltration can exceed this GAD-enhancing margin by 6–14 mm [5]. A minimum 1-cm margin would balance maximal tumor resection with safety. Given the pattern of tumor cell invasion typically follows white matter tracts, resection beyond the margin of GAD enhancement up to a sulcal boundary or up to the ventricle wall will be accepted for the intervention arm, even if < 1 cm.

#### Criteria for discontinuing or modifying allocated interventions

At their own discretion, participants may withdraw from the study at any time and for any reason. Study participants may also be withdrawn from the study at the discretion of an investigator for reasons such as, but not limited to safety, participant compliance or behavioral concerns. All participants need to have a confirmed final pathological diagnosis of high-grade glial tumor (i.e., grade 3 or higher) to be included in the primary intention-to-treat (ITT) analysis. Participants with any other final diagnosis will not remain in the study, but data will be collected to provide additional safety information.

#### Strategies to improve adherence to interventions

In order to increase the relevance of the trial design to patients, and to increase the likelihood of patient participation, we have identified a patient volunteer who has agreed to meet quarterly to oversee all aspects of research conduct and manage any challenges. We anticipate involvement of a patient stakeholder will specifically enhance the framing of the question, approach to patients and family, nuances in adherence to protocol, and providing support from the beginning to the end for patients.

#### Relevant concomitant care permitted or prohibited during the trial

Use and dose of antiepileptic medications and dexamethasone will be collected. There are no restrictions on concomitant medications, unless they result in preclusion from surgery (e.g., anti-coagulants). Prior chemotherapy or radiation for a brain lesion is not permitted.

### Outcomes

#### Primary feasibility outcome

The primary feasibility outcome is the number of patients enrolled and successfully allocated to the study interventions per year during the duration of the pilot RCT at each study center. This number will determine whether a larger phase III RCT is warranted and feasible.

#### Secondary outcomes

*Feasibility:* (1) Among all eligible patients, the proportion of patients (i) consenting to participate and (ii) completing all scheduled follow-up assessments. Reasons for non-enrollment of all eligible patients will be recorded (e.g., physician refusal, patient’s preference, inability to meet study timelines). (2) The proportion of patients in each group receiving the assigned extent of surgical resection according to the randomized allocation, as assessed by the volume of residual contrast enhancement in 1st post-operative MRI and compared to the preoperative MRI. Due to the pragmatic nature of this trial, we use intention to treat as a measure of supramaximal resection intent. We expect that as a group, these patients should have less enhancing residual volume in post-operative imaging. Reasons for failure to receive the assigned extent of surgical resection will be recorded (e.g., physician refusal, technical challenges).Preliminary *efficacy:* Assessment of the (1) overall survival and (2) progression-free survival based on the Modified Response Assessment in Neuro-oncology (mRANO) criteria [21]. The date of death will be obtained from hospital records, outpatient follow-up clinic notes, or provincial cancer registries. Progression-free survival will be measured based on the mRANO criteria [21] during regular interval clinical and MRI follow-up (according to each institution’s established practice) until death or 12 months after surgery.
*Safety:* (1) National Institute of Health Stroke Scale (NIHSS), (2) mRS, (3) EQ-5D, and (4) 30-day all-cause mortality. Utilizing three independent scales for the assessment of morbidity will ensure that we capture any objective neurological deficits along with their impact on function and quality of life. It will be critical to ensure that a supra-marginal resection does not lead to an increased 30-day mortality rate, which is a time frame that is most likely to be related to adverse surgical events.

Specifically, we will measure the changes at each assessment relative to preoperative baseline values in the following scales:

The NIHSS at days 2 ± 1 and 30 ± 5 after surgery (conducted during in-person follow-up). The NIHSS is a validated tool for measuring neurological outcomes that was originally developed for rapid grading of stroke symptoms but has since been adopted in surgical clinical trials [9].The mRS (assessed either in-person or over the phone) at 6 and 12 months after surgery. The mRS provides a measure of global disability and has been widely used to assess the outcomes after stroke and other neurological problems. The scale consists of six grades from 0 (no symptoms) to 5 (severe disability); 6 indicates death [22].The EQ-5D (assessed either in-person or over the phone) at 6 and 12 months after surgery. The EQ-5D is a generic instrument used to measure health-related QOL, designed for self-completion by respondents (face-to-face or over telephone interview, also available in proxy version through caregiver). It has five dimensions: mobility, self-care, usual activities, pain or discomfort, and anxiety or depression. This tool rates the impact of disease on a scale of 0 to 1 with a lower score indicating a greater effect on the health.Where feasible, we will also attempt neuropsychological assessments pre- and post-operatively to detect the subtle differences potentially attributable to a supra-marginal resection.

iv)Health economics: The future definitive RCT will also assess the incremental cost-effectiveness ratio at 6 months. This will be analyzed to determine whether a supra-marginal resection has the potential to decrease societal costs in the long term. Cost data will be collected, in addition to the quality of life (EQ-5D) at 6 and 12 months, which would enable the calculation of the incremental cost-utility ratio (ICUR) of the two interventions. We plan to conduct a full-scale health economic analysis in the future large-scale trial, based on both direct (e.g., operating room, nursing, inpatient hospital stay) and indirect costs (e.g., potential loss of income) costs. Utilities will be calculated based on the EQ-5D, and cost-utility will be based on the perspective of the “idealized insurer”/third-party payer (e.g., the provincial government payer). Given the short survival of HGG patients, discounting will be at 1% with provisions for subgroup analyses.

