### Schedule of events

**Table Taba:** 

Evaluation	14 days prior to surgery/randomization (screening/enrollment)	Day 0: surgery day (randomization)	Days 1–3: post-OP 1^**st**^ assessment	Day 30 (± 5 days) 2^**nd**^ assessment	6 months (± 2 weeks) post-surgery 3^**rd**^ assessment Collect outcomes	12 months (± 1 month) post-surgery	24 months: annually after (until death, completion of the pilot phase, or lost to F/U)
*Eligibility criteria, medical history, demographics*	X						
*Neurological exam (NIHSS)*	X		X	X			
*MR scan*	X^1^			X ^1^	X^1^	X^1^	X^1^
*Concomitant meds (steroid/antiepileptic)*	X			X	X		
*Received randomly assigned treatment*		X					
*Pathology report*				X			
*Surgical report*				X			
*Adverse surgical* adjuvant tx** events*			X*	X*	X**	X**	X**
*Outcome assessment (clinical secondary outcomes) (EQD-5-mRS)*					X	X	X
*Death*				X	X	X	X
*Progression free survival*				X	X	X	X
*Timing of RTX*				X	X	X	X
*Timing of chemotherapy*				X	X	X	X

*These adverse events only relate to surgery

**These adverse events only relate to adjuvant radiation and/or chemotherapy

^1^These images are obtained through routine clinical practice

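### Residual contrast enhancement alone cannot show whether the assigned extent of resection was delivered, because both arms share the same target for enhancing tumour

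*Protocol article*

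**What the plan says.** **Outcome.** Under Secondary outcomes (Feasibility, item 2), the protocol article will report "The proportion of patients in each group receiving the assigned extent of surgical resection according to the randomized allocation". The yardstick for this is imaging, with receipt of the operation taken "as assessed by the volume of residual contrast enhancement in 1st post-operative MRI and compared to the preoperative MRI". It adds that "we use intention to treat as a measure of supramaximal resection intent", and of the supra-marginal arm it says: "We expect that as a group, these patients should have less enhancing residual volume in post-operative imaging". Reasons for not receiving the assigned extent are to be recorded, with refusal by the physician and technical difficulty as examples.

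**Arms.** Under Explanation for the choice of comparators, the control operation is a "planned resection extending only to ≥ 95% of the GAD-enhancing regions of the tumor without expanding the resection beyond this margin". The intervention goes beyond the same 95% of the enhancing region, "to either at least 1 cm into non-enhancing tissue or to the nearest non-enhancing sulcal boundary/ventricle wall" where such a structure is nearer than 1 cm.

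**Other information on delivery.** The Schedule of events has a Day 0 item, "Received randomly assigned treatment", and collects the surgical report. Under Concealment mechanism, a surgical documentation template leaves out the allocation.

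**Use of the result.** Under Adherence to protocol, successful adherence means completed assessments and ascertained survival. Progression to phase III depends on recruitment and on the DSMB raising no concern that cannot be rectified. The same section sizes phase III at 247 deaths for a hazard ratio of 0.7, says pilot data will inform the sample size, and plans to carry pilot patients into that trial if the protocol does not change much.

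**The concern.** The outcome asks whether each patient had the operation to which they were randomised. The measure looks at tissue that both operations are meant to remove, and not at the tissue that separates them. High apparent adherence in both arms would therefore be compatible with clear separation between the arms, with partial separation, or with none.

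This matters because delivery is uncertain on the article's own account: practice follows individual surgeon preference, surgeons cannot be blinded, and refusals and technical failures are expected. A pilot is the natural place to learn how far the two arms really differ. If that is not measured, the phase III sample size is set without knowing how much the treatment contrast is diluted.

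**Working it through.** **Step 1. Compare the arm definitions with the measure.** The 95% cut-off for classifying a patient is an assumption taken from the arm definitions; the outcome text states none.

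| Operation performed | Residual enhancement | Assigned extent received, if assigned supra-marginal | Assigned extent received, if assigned marginal |
|---|---|---|---|
| Under 95% of enhancement cleared | high | no | no |
| At least 95% cleared, stops at the margin | low | no | yes |
| At least 95% cleared, plus 1 cm or to sulcus/ventricle | low | yes | no |

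Row 1 is detectable. Rows 2 and 3 can give the same reading, yet the correct answers are opposite. A different cut-off does not help: any rule based only on residual enhancement treats two patients with the same residual alike, whatever was removed beyond the margin.

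**Step 2. Direction of error.** Let g be the share of an arm with at least 95% clearance, and q the share that truly received the assigned extent. Clearance is necessary in both arms, so q ≤ g. The measure reports g. Apart from imaging error it can overstate adherence but not understate it, and q may lie anywhere from 0 to g.

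**Step 3. Scale of what is not observed.** Assume a spherical tumour of diameter D with a full 1 cm rim, and r = D/2.
- Rim volume = (4/3)π[(r+1)³ − r³]
- Permitted enhancing residual = 0.05 × (4/3)πr³
- D = 3, 4, 5 cm: rim about 51, 80, 114 mL; permitted residual about 0.7, 1.7, 3.3 mL

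Real rims will often be smaller because of the sulcal and ventricular exception. The point is only that the separating tissue is large and the measure does not look at it.

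**Step 4. Reproduce the plan's figure.** Deaths by Schoenfeld's formula with 1:1 allocation:
- D = 4(1.96 + 0.8416)²/(ln HR)²
- HR 0.7: 31.40/0.1272 = 246.8, so 247. This matches the article.

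**Step 5. Illustrate dilution.** Let f be the share of the supra-marginal arm given only a marginal resection, and c the share of controls resected beyond the margin. The documents give neither, so the values below are assumptions. Use HR_eff = exp[(1 − f − c) ln 0.7].

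| f | c | HR_eff | Deaths for 80% power | Power with 247 deaths |
|---|---|---|---|---|
| 0 | 0 | 0.700 | 247 | 80% |
| 10% | 0 | 0.725 | 305 | 71% |
| 10% | 10% | 0.752 | 386 | 61% |
| 20% | 10% | 0.779 | 504 | 50% |
| 20% | 20% | 0.807 | 686 | 39% |

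**Step 6. What a valid measure could tell the pilot.** With 36 per arm, 32 of 36 adherent (89%) would have an exact 95% confidence interval of about 74% to 97%. That is wide, but it would exclude widespread non-delivery in that arm.

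**The case against.** **Other sources exist.** Reasons for failure, the Day 0 item and the surgical report all bear on delivery, and a template that omits the allocation need not omit the extent resected. This stands in part. A reader might infer that the pilot has no means of detecting non-delivery, and the documents do not support that. But these sources are site-reported and the article attaches no margin criterion to them. They are unlikely to show reliably an unreported shortfall or an over-resected control.

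**The measure is not empty.** It detects gross under-resection, and because controls may keep some enhancing residual, a group difference is plausible. Both points stand. A group difference still does not classify patients, and less residual enhancement does not show that a margin was taken.

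**The trial is pragmatic and analyses intent.** The arms are defined as planned resections, so incomplete delivery is part of the effect of the strategy. That justifies the intention-to-treat comparison of outcomes. It does not supply the separate outcome promised here, which concerns what was received; an analysis principle does not measure that.

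**The consequences are hypothetical.** A reader might infer that phase III is underpowered as planned. The documents do not support this either: they give no crossover rates, they describe a hazard ratio of 0.7 as the improvement desired, and they say the sample size will be estimated from pilot data. Step 5 shows sensitivity and is not a forecast.

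**It is a minor outcome.** This is one descriptive secondary outcome, absent from the progression criteria. That stands and limits the severity. The mismatch is nevertheless not a detail left to another document, because the article states the measure and it does not fit the article's own arm definitions.

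**Conclusion.** The point holds in a limited form. Residual enhancement alone cannot distinguish a supra-marginal from a marginal resection, so the stated measure would return the proportion with adequate clearance of enhancing tumour rather than the proportion who received the assigned extent. This follows from the article's definitions and needs no outside figure. Only the upper-bound reading relies on applying the 95% target as the cut-off.

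The size of any overstatement is unknown, since true delivery is unknown. The range of 305 to 686 deaths against 247 rests entirely on assumed crossover of 10 to 40 percentage points in total, and on proportional dilution of the log hazard ratio. The primary feasibility outcome, the pilot's sample size and the progression criteria are not affected. Severity: should fix.

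**What to change.** In the Secondary outcomes text, define receipt of the assigned extent from the arm definitions the article already gives, using the preoperative and first post-operative MRIs:
- **Both arms:** at least 95% of the preoperative enhancing volume removed.
- **Supra-marginal arm, in addition:** the post-operative cavity, compared with the preoperative enhancing edge, reaches the protocol's 1 cm margin or its sulcal or ventricular exception.
- **Control arm, in addition:** the cavity does not extend beyond the enhancing edge.
- **Tolerance:** apply both margin comparisons within a measurement tolerance stated in advance.

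Keep residual enhancement as a separate measure of gross total resection. Report the proportion per arm with a 95% confidence interval, and the between-arm difference in margin. Use this delivered separation when sizing phase III. It need not become a new go/no-go threshold, for which the documents offer no basis.

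**Cost.** A wording change and image analysis of about 72 scan pairs; no additional scans and no change to treatment. The work is not wholly covered by existing plans, because the Participant timeline mentions central review only for additional post-operative MRIs. Brain shift and cavity collapse will add measurement error against a 1 cm margin, which is why the tolerance must be fixed beforehand.
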